### Endpoints and follow-up

The primary endpoint is the NPPV failure rate, defined as the need for endotracheal intubation and invasive ventilation at any point during the study. Secondary endpoints include decrement of PaCO_2_ from baseline to 2 h after randomization, hospital mortality, 28-day mortality, and 90-day survival, as well as actual intubation rate, intensive care unit (ICU) admission, hospital stay, hospital costs, ventilator-free days within 28 days, hospital-free days within 90 days, and 90-day hospital readmission.

All patients will be monitored until hospital discharge or until day 90 in cases where the patients remain at the hospital. After discharge, follow-up will be performed by phone on days 28 and 90 after randomization, and the following will be recorded: 28-day mortality, ventilator-free days within 28 days, hospital-free days within 90 days, 90-day survival, and 90-day hospital readmission.

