### Statistical analysis

We will report continuous variables as means ± standard deviations or medians and interquartile ranges, when appropriate, and categorical variables as proportions.

Continuous variables will be compared using an appropriate parametric (Student’s *t* test) or nonparametric (Mann–Whitney *U* test) method. Categorical variables will be compared using a chi-square test or Fisher’s exact test, if appropriate. A linear mixed model with two factors (study group and time) will be used to analyze variables repetitively measured over time; Bonferroni’s adjustment for multiplicity of tests will be used in post hoc comparisons to ensure that the total error rate will not exceed 0.05.

We will use a chi-square test or Fisher’s exact test to compare the primary outcome and secondary dichotomous outcomes, and a parametric (Student’s *t* test) or nonparametric (Mann–Whitney *U* test) method to compare secondary continuous outcomes, as appropriate. For the primary and secondary outcomes, we will calculate between-group differences in risk for dichotomous outcomes, between-group median differences (using Hodges–Lehmann estimates) for continuous outcomes with non-normal distributions, and between-group mean differences for continuous outcomes with normal distributions, all with 95% confidence intervals. The baseline characteristics will be tested for imbalance. If imbalances are found (despite the 1:1 randomization of a relatively large cohort), the primary and secondary outcome variables will be analyzed using a multiple logistic regression model, adjusted for possible baseline imbalances.

Cumulative event rates for the primary and secondary endpoints involving time-to-event data will be estimated for the two groups using the Kaplan–Meier method and compared using a log-rank test. Hazard ratios, their 95% confidence intervals, and *P* values for the comparison of the two treatment groups will be determined using the Cox regression model.

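### Kaplan–Meier rates for need for intubation, with event-free deaths censored, overstate NPPV failure: slightly from death alone, possibly materially if discharge is also censored

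*Protocol article*

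**What the plan says.** The Statistical analysis section sets out two analyses that can both apply to the primary endpoint.

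- **Proportions:** "We will use a chi-square test or Fisher’s exact test to compare the primary outcome and secondary dichotomous outcomes", with a between-group risk difference and 95% confidence interval.
- **Time to event:** "Cumulative event rates for the primary and secondary endpoints involving time-to-event data will be estimated for the two groups using the Kaplan–Meier method". A log-rank test follows, and hazard ratios "for the comparison of the two treatment groups will be determined using the Cox regression model".

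No competing-event method is named, and no censoring rule is given for death or for discharge.

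The Endpoints and follow-up section defines NPPV failure as the "need for endotracheal intubation and invasive ventilation at any point during the study". On observation it says: "All patients will be monitored until hospital discharge or until day 90 in cases where the patients remain at the hospital". It continues: "After discharge, follow-up will be performed by phone on days 28 and 90 after randomization". The items listed for those calls are "28-day mortality, ventilator-free days within 28 days, hospital-free days within 90 days, 90-day survival, and 90-day hospital readmission". Need for intubation is not among them.

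**The concern.** Kaplan–Meier treats a censored patient as someone who could still have the event later, at the same rate as those still under observation. That suits a patient lost to follow-up. It does not suit a patient who has died without being intubated, whose later risk of intubation is zero. With such deaths censored, one minus Kaplan–Meier estimates the failure risk in a setting where nobody dies first, not the share of patients in whom NPPV fails.

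The plan would then carry two cumulative rates for the same endpoint in the same patients: the crude proportion, and a curve that ends above it. The curve would also overstate the absolute difference between the arms. For 28-day and 90-day survival there is no such problem, because death is the event.

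Discharge raises a related question. Patients sent home have recovered, so censoring them at discharge would be informative, and the effect could be much larger than that of death.

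**Working it through.** **Inputs from the article** (Sample-size calculations and interim analyses): failure proportions of 15% (low intensity) and 6% (high intensity), 9 points apart. The article gives no cumulative-incidence figure to reproduce. It also gives no event-free death rate, time to intubation or length of stay, so those below are assumptions.

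**Step 1: death censored, discharged patients kept event-free to day 90.** Let F be the proportion with the event and D the proportion who die without it. With proportional cause-specific hazards, the event carries a share F/(F+D) of the total hazard, so

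1 − KM = 1 − (1 − F − D)^(F/(F+D)).

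| Assumed D | F = 15% | F = 6% |
|---|---|---|
| 1% | 1 − 0.84^0.9375 = 15.1% | 1 − 0.93^0.857 = 6.0% |
| 5% | 1 − 0.80^0.75 = 15.4% | 1 − 0.89^0.545 = 6.2% |
| 10% | 1 − 0.75^0.60 = 15.9% | 1 − 0.84^0.375 = 6.3% |

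The excess is about 0.4 points or less when D is at most 5%, and about 0.9 points in the low-intensity arm at D = 10%. If deaths fall mostly after the intubations it is smaller: simulated curves with D = 5% end at 15.1–15.4%.

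**Step 2: discharge also censored.** Among patients without the event, let S_L(t) be the proportion not yet discharged. Let f(t) and S(t) be the density and survivor function of time to intubation among those intubated. The hazard that Kaplan–Meier sees is

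h(t) = F·f(t) / [F·S(t) + (1 − F)·S_L(t)], and 1 − KM at day 28 = 1 − exp(−∫h).

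As recovered patients leave, the denominator shrinks and each later intubation weighs more. A simulation of 400,000 patients per arm, with no deaths, gave at day 28:

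| Mean time to intubation | Mean stay | Low | High | Difference |
|---|---|---|---|---|
| 2 days | 14 days | 15.4% | 6.1% | 9.2 points |
| 2 days | 10 days | 15.9% | 6.4% | 9.6 points |
| 4 days | 14 days | 17.7% | 7.1% | 10.7 points |
| 4 days | 10 days | 26.7% | 10.7% | 16.0 points |

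(Differences were taken before rounding.) Evaluating the integral directly, with exponential time to intubation and a gamma stay of shape 4, gives 15.3–25.9% versus 6.1–10.7% over the same grid. An exponential stay gives 17.3–23.4% versus 7.0–9.7%. The exact range therefore depends on the assumed shape as well as the means, and it widens if intubations occur later.

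**Step 3: the alternative.** Aalen–Johansen, with event-free death competing and discharged patients kept event-free to day 90, gives 15.0% and 6.0%, 9.0 points apart. Apart from patients lost or withdrawn before day 90, this equals the crude proportions.

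**Step 4: readmission, only if analysed as time to event.** The formula in step 1, with assumed F of 20–40% and D of 3–15%, gives an excess from 0.3 points (1 − 0.77^0.870 = 20.3%) to 4.1 points (1 − 0.45^0.727 = 44.1%).

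**The case against.** The strongest reply is that little of consequence is affected. The primary comparison is a test of two proportions with a risk difference, and the sample size rests on two proportions. The curve is supplementary. Patients with a do-not-intubate order are excluded at entry, which limits event-free death. The endpoint is also the need for intubation, so a patient who meets the criteria but is not intubated may still count. Finally, censoring rules are often left to an analysis plan, and none is shown.

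Most of this stands and limits the size of the point. It does not remove it. The article goes beyond leaving the method open: it names Kaplan–Meier for the primary endpoint. Intubation needs consent from next of kin or a surrogate, so death without it remains possible.

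Four stronger readings are tempting, and the document supports none of them.

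- **Discharge is a censoring time.** A reader might infer this from the phone list. The article never says so. The endpoint runs through the whole study, contact continues to day 90, and last observation carried forward, the stated rule for missing data, could keep a discharged patient event-free.
- **The curve would show about 34% versus 16%.** Censoring at discharge with constant hazards and a 10-day mean time to any exit gives 1 − exp(−0.15 × 28/10) = 34.3% and 1 − exp(−0.06 × 28/10) = 15.5%. Besides the unstated censoring rule, this puts only 1 − exp(−0.2) = 18% of intubations in the first 48 hours. That is hard to assume here, although the article gives no timing.
- **Readmission will be analysed by Kaplan–Meier.** It is listed only as a 90-day endpoint and may be treated as dichotomous.
- **The log-rank test is invalid.** With competing events censored it remains a valid test of equal cause-specific hazards.

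**Conclusion.** The point holds in a limited form. The named estimator is the wrong one for cumulative need for intubation, because event-free death precludes the event. With such deaths censored, the curve can only match or exceed the crude proportion. From death alone the excess is a few tenths of a point, up to about 0.9 points in the low-intensity arm, assuming 5–10% event-free deaths and proportional cause-specific hazards. The larger figures, up to 26.7% versus 10.7% at day 28, apply only if discharged patients are censored at discharge. The article leaves that open but does not state it, and the figures rest on assumed timings. Readmission is affected only if it is analysed as time to event.

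The primary test, the risk difference and the sample size are untouched. The change is worth making because it affects the planned cumulative display of the primary endpoint and is easy to put right.

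**What to change.** In the Statistical analysis section:

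1. Keep Kaplan–Meier for 28-day and 90-day survival.
2. For need for intubation, and any other non-fatal endpoint analysed over time, report Aalen–Johansen cumulative incidence with event-free death as a competing event.
3. State that patients discharged alive without intubation are carried as event-free to day 90, or that discharge is a competing event, and that they are not censored at discharge. The curve then agrees with the primary proportion.
4. Keep log-rank and Cox if wanted, labelled as cause-specific comparisons. Gray's test is an optional addition, since it answers a different question.

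The cost is a few lines of text and possibly a second software package beside the one named. No new data are needed, because deaths and hospital stay are already recorded. The reported cumulative rates will be slightly lower than the Kaplan–Meier ones. The primary endpoint, its test and the sample size do not change.

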### Study dropouts

Because participation is voluntary, patients have the right to withdraw consent to participate at any time for any reason, without any unfavorable consequences for further medical treatment. Furthermore, investigators have the right to terminate the participation of any patient at any time if the investigator deems it to be in the participant’s best interest. The reasons and circumstances for study discontinuation will be documented in the CRF.

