### Sample-size calculations and interim analyses

The calculation of the sample size was based on our primary hypothesis that in AECOPD patients high-intensity NPPV leads to a reduced need for endotracheal intubation compared to low-intensity NPPV. Our previous clinical experience and previous studies [18–20] led us to anticipate that the need for endotracheal intubation would be 15% for the low-intensity NPPV group. Based on the assumption that the need for intubation could be reduced to 6% in the high-intensity NPPV group, we estimated that a minimum sample size of 480 patients would be required to detect a between-group difference of 9% for the need for intubation, with an 81% power and a two-tailed alpha level of 0.05, using superiority tests for two proportions. Assuming a dropout rate of 20%, we calculated that 600 patients should be enrolled.

Interim analysis to assess superiority is scheduled, and it will take place at hospital discharge of the first 300 randomized patients. The criteria for premature discontinuation of the study, based on the results of this single interim analysis, will be those defined by O’Brien and Fleming [34]. It will be performed at the coordinating center by an independent data and safety monitoring board (DSMB). The DSMB will meet by conference call, and DSMB discussions will take place by email or conference call.

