In case of loss to follow-up or consent withdrawal, the causes will be reported. Intention-to-treat (ITT) and per protocol (PP) analyses will be conducted. For the ITT analysis, data will be processed for all trial patients in the groups in which they were randomized. A PP analysis will be performed as a sensitivity analysis in the case of any loss to follow-up, a missing primary endpoint, or any protocol deviation that might lead to a biased conclusion. Missing data will be handled using the “last observation carried forward” method.

All tests will be two-sided. Differences with *P* values of less than 0.05 will be considered statistically significant, except for those incorporating multiple comparisons. Statistical analyses will be performed using SPSS software (version 19.0, SPSS Inc., Chicago, IL, USA).

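### Last observation carried forward, applied to every endpoint, scores patients lost before the event as not intubated or alive; the size and direction of the resulting bias cannot be fixed from the protocol

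*Protocol article*

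**What the plan says.** The Statistical analysis section of the protocol article gives one rule for missing data: "Missing data will be handled using the “last observation carried forward” method". It is not limited to repeated measurements. In the intention-to-treat analysis, "data will be processed for all trial patients in the groups in which they were randomized", so all randomized patients stay in the denominator. The section foresees that the primary endpoint itself may be missing, and the back-up it names is per protocol: "A PP analysis will be performed as a sensitivity analysis in the case of any loss to follow-up, a missing primary endpoint".

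The primary endpoint (Endpoints and follow-up) is binary and counts an event at any time in the study. It and the dichotomous secondary endpoints are compared by chi-square or Fisher's exact test, with a risk difference. Separately, the plan has a linear mixed model for repeated measures, and Kaplan–Meier, log-rank and Cox analyses for time-to-event endpoints.

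On dropout, the sample-size section says "Assuming a dropout rate of 20%, we calculated that 600 patients should be enrolled". Under Study dropouts, patients may withdraw and "investigators have the right to terminate the participation of any patient at any time". The Discussion accepts that investigators cannot be blinded.

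**The concern.** Carrying the last value forward presumes that a patient's state would not have changed. For an event that happens once, the last state seen before an event-free dropout is always the favourable one, so the rule imputes success with certainty. It does so for intubation and for crude mortality. For PaCO2 at 2 h it carries the baseline value forward and records no change.

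This bears on the primary test. The plan allows for 120 dropouts (20% of 600), while its own rates imply about 63 primary events (0.15 × 300 + 0.06 × 300 = 45 + 18). If even part of that allowance becomes missing primary outcomes, the imputed values carry real weight. Because unblinded investigators can end participation, dropout could be related to arm and to deterioration, and in that setting the rule does not even bias in a known direction.

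**Working it through.** **Inputs from the protocol article.** Control rate: "the need for endotracheal intubation would be 15% for the low-intensity NPPV group". High-intensity rate: "the need for intubation could be reduced to 6% in the high-intensity NPPV group". Dropout allowance 20%; 600 patients at 1:1, so 300 per arm; two-sided alpha 0.05.

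**Inputs that are assumptions.** The share *f* of dropouts' event risk that falls after they leave; the split of dropout between arms; the event risk *r* after dropout.

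**The plan's own figure.** The dropout step reproduces: 480 / (1 − 0.20) = 600. (The 480 for 81% power does not follow from the usual two-proportion formula, which gives 372, or 416 with continuity correction. That is a separate matter and does not enter here.)

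**Step 1: equal dropout, true effect as planned.** A dropout with no event so far is coded 0, so the expected observed rate is p × (1 − 0.20 × *f*). Power is for the pooled z-test with 300 per arm.

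| *f* | Low intensity | High intensity | Difference | Power |
|---|---|---|---|---|
| 0 (nothing missed) | 15.0% | 6.0% | 9.0 points | 95.1% |
| 25% | 14.25% | 5.7% | 8.55 points | 93.9% |
| 50% | 13.5% | 5.4% | 8.1 points | 92.6% |
| 100% | 12.0% | 4.8% | 7.2 points | 89.1% |

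The bottom row assumes that dropouts carry their whole event risk after leaving, in effect that they leave at randomization. The risk ratio stays at 0.40 (4.8 / 12.0 = 6 / 15). With no true effect and equal dropout, both arms are understated alike and the rejection rate stays at 5%.

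**Step 2: unequal dropout, no true effect.** Both arms have a true rate of 15%. The expected observed rate is 0.15 − *d* × *r*, where *d* is the arm's dropout. Rejection is two-sided by the pooled z-test, 300 per arm.

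| Dropout | *r* | Observed rates | False difference | Rejection |
|---|---|---|---|---|
| 17% vs 23% | 15% | 12.45% vs 11.55% | 0.9 points | 6.3% |
| 17% vs 23% | 30% | 9.9% vs 8.1% | 1.8 points | 12% |
| 17% vs 23% | 50% | 6.5% vs 3.5% | 3.0 points | 39% |
| 15% vs 25% | 15% | 12.75% vs 11.25% | 1.5 points | 8.7% |
| 15% vs 25% | 30% | 10.5% vs 7.5% | 3.0 points | 25% |
| 15% vs 25% | 50% | 7.5% vs 2.5% | 5.0 points | 80% |

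The arm that loses more patients always looks better. Swapping the arms reverses the sign.

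**Step 3: how much of this comes from the rule itself.** Where dropouts carry average risk (*r* = 15%), the patients who stay show 12.75 / 0.85 = 15% and 11.25 / 0.75 = 15%. Observed data are then unbiased, and carrying forward creates the whole 1.5-point difference. Where *r* = 30%, the stayers show 10.5 / 0.85 = 12.4% and 7.5 / 0.75 = 10.0%. Informative dropout then also biases an analysis of the observed patients, so the higher rejection rates are not due to the rule alone. They show that it gives no protection, and that any replacement needs a sensitivity analysis.

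**Step 4: the named back-up.** A per-protocol analysis compares a selected set of patients. It does not vary the value given to a missing outcome among all randomized patients, so it cannot show whether the result depends on the carry-forward assumption.

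**The case against.** Several stronger readings are tempting, and the document does not support them.

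- **Every dropout is counted as a success.** No. A patient intubated before leaving keeps the event. Only those lost before the event are affected.
- **One fifth of primary outcomes will be missing.** The 20% is a sample-size allowance. Patients are followed to discharge or day 90, then telephoned on days 28 and 90, and sites are queried for missing data. Intubation for an acute exacerbation would be expected mostly in hospital, so its actual missingness may be far lower.
- **The rule favours high intensity because higher pressure drives patients out.** Both arms are titrated to tolerance, and the Background expects better comfort and tolerance with high intensity. It also describes intolerance of conventional NPPV as ending in intubation, which is an observed event, not a missing one. Stopping NPPV is not the same as leaving the study. No direction can be inferred.
- **The rule contradicts the mixed model and the survival analyses.** Nothing says that carried-forward values feed these models. What remains is uneven handling: the same lost patient could be a survivor in a 28-day mortality test and censored in a survival curve.
- **The per-protocol set drops exactly the patients with missing data.** That set is not defined in the article, so this cannot be asserted.

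It is also fair that the equal-dropout case is conservative, with power still 89.1% or more, and that the larger rejection rates need assumed dropout splits and, above 15%, assumed excess risk. All of this limits the size of the problem. None of it makes the rule suitable for a once-only event.

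**Conclusion.** The point holds as a fault in a stated rule. For the primary endpoint and for crude mortality, carrying the last observation forward imputes the favourable outcome to every patient lost before the event and biases event rates downward. Under equal dropout the cost is a smaller risk difference, between 8.55 and 7.2 points instead of 9.0 at 20% dropout for *f* from 25% to 100%, with type I error intact. Under unequal dropout false positives can rise in either direction, from about 6% to 80% over the range examined. The upper end requires a 10-point imbalance and a 50% event risk among dropouts, which is extreme. The dropout split, the post-dropout risk and the timing are all assumptions, and the document gives no rate of missing primary outcomes, so neither the size nor the direction of the bias can be determined from it.

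**What to change.** Delete the carry-forward sentence and replace it with rules by endpoint:

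1. Keep recording intubation and vital status after the intervention or participation stops, unless consent for data use is withdrawn.
2. For a missing primary endpoint, use multiple imputation by arm from baseline and 2–48 h data, with a tipping-point or worst-case sensitivity analysis on all randomized patients.
3. State that the planned mixed model uses the observed repeated measures without filling in values.
4. State that survival analyses censor at last known contact.
5. Keep the per-protocol analysis if wanted, but do not present it as the remedy for missing data.

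The change should be fixed before any unblinded comparison, the interim analysis included. The cost is a change of wording and a little more analysis work. The 2–48 h measurements and the day 28 and day 90 calls are already planned; only follow-up after withdrawal needs clearer wording.

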### Trial organization

Appendix 1 lists the investigators of the HAPPEN collaboration group. The steering committee is composed of the principal investigators in the study, who all contributed to its design and approved the final protocol (Appendix 2). The executive committee is made up of the main investigators at each participating center and is responsible for administrative, trial, and data management (Appendix 2). When the report on the results of the trial is submitted for possible publication, each study center will be eligible for one co-authorship, plus a further co-authorship for every 20 patients with complete datasets.

The DSMB is composed of three external, independent experts in critical care medicine, NPPV, and COPD (Appendix 2). At the interim analysis, using the general data provided by the three internal members, it will recommend the continuation or discontinuation of the trial, based on the available data from the interim analysis. The DSMB will be responsible for monitoring patient data and safety, including review of the protocol, with emphasis on data integrity and participant risk and safety issues, monitoring adverse events (including suspected severe adverse reactions), and monitoring the overall status of the study (e.g., progress of patient enrollment, general adherence to protocol, and completeness of data entry).

The trial management team includes a chief investigator, a project manager, a statistician, a clinical epidemiologist, and an investigator expert in clinical trials (Appendix 2). The responsibilities of this team are as follows:Planning and conducting the study: designing the protocol and CRF, designing the investigator manual, and managing and controlling data qualityResearch center support: assisting the centers with administrative submission, monitoring recruitment rates, providing sealed randomization envelopes, taking actions to increase patient enrollment, monitoring follow-up, auditing, and sending study materials to the research centersProducing a monthly study newsletter and developing supporting material for the studyProgramming a research-in-progress meeting at least once every 6 months with the principal investigators from all sitesStatistical analysis and research reporting: interim and complete statistical analysis and helping to write the final manuscript.

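### The final primary test is set at P < 0.05 although an O'Brien–Fleming superiority look precedes it, so overall error slightly exceeds 5%; separately, two sections disagree on who runs that look

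*Protocol article*

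**What the plan says.** **Interim look.** The section on sample size and interim analyses plans one look for superiority, when the first 300 randomized patients have been discharged. The criteria for stopping early, "based on the results of this single interim analysis, will be those defined by" O'Brien and Fleming. No numerical level is given for the interim or the final analysis.

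**Design error rate.** The same section sizes the trial "with an 81% power and a two-tailed alpha level of 0.05, using superiority tests for two proportions".

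**Decision rule.** The Statistical analysis section states "All tests will be two-sided" and then that P "values of less than 0.05 will be considered statistically significant, except for those incorporating multiple comparisons". The only multiplicity procedure described there is Bonferroni, for post hoc comparisons in the repeated-measures model. The primary outcome is compared by chi-square or Fisher's exact test.

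**Who performs the look.** On the interim analysis, the sample-size section says "It will be performed at the coordinating center by an independent data and safety monitoring board". Trial organization lists among the trial management team's duties "interim and complete statistical analysis and helping to write the final manuscript". That team includes the chief investigator, the project manager and a statistician. Trial organization also has three internal members supply the data that the DSMB uses at the interim, and the text shown does not say who they are.

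**The concern.** O'Brien–Fleming is a pair of critical values that together hold the overall error at 5%. The article applies it to stopping early and then gives 0.05 as the general level. Taken literally, the final primary test is run at the full 0.05 after a look that has already used part of the error. A final P just under 0.05 would then be positive under the Statistical analysis section and negative under the O'Brien–Fleming design. That should be settled before the data are seen.

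The second matter is governance. Treating investigators know the allocation, and the attending physician makes the final decision to intubate, which drives the primary endpoint. The trial management team monitors recruitment and acts to increase it. If people running the trial learned the interim difference, that knowledge could affect the second half. The article should therefore give one answer on who performs the analysis.

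**Working it through.** **Inputs from the protocol article.** Two-sided 0.05; one look at 300 of 600; 1:1 allocation; control rate ("the need for endotracheal intubation would be 15% for the low-intensity NPPV group") and experimental rate ("the need for intubation could be reduced to 6% in the high-intensity NPPV group"); 480 evaluable, 600 enrolled; chi-square or Fisher's exact test.

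**1. The plan's own figures.** The dropout step reproduces: 480/(1 − 0.20) = 600. The 480 does not. With p̄ = (0.15 + 0.06)/2 = 0.105, n per arm = [1.960·√(2·0.105·0.895) + 0.878·√(0.15·0.85 + 0.06·0.94)]² / 0.09² = 186, or 372 in total. This is a separate matter and does not enter the error calculation.

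**2. Information at the look.** t = 300/600 = 0.50. If dropout is even over time, 240/480 gives the same. The extreme case, with all 300 evaluable but only 480 at the end, is t = 300/480 = 0.625.

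**3. Boundaries that hold 5%.** Under no difference, Z₁ and Z₂ are bivariate normal with correlation √t. Overall error = P(|Z₁| > c₁ or |Z₂| > c₂).
- Classical O'Brien–Fleming: c₁ = c/√t, c₂ = c. Setting the error to 0.05 at t = 0.50 gives c = 1.977, so c₁ = 1.977·√2 = 2.797.
- Lan–DeMets O'Brien–Fleming type: error spent by t is 4[1 − Φ(2.241/√t)], which is 0.0031 at t = 0.50, so c₁ = 2.963; solving for the rest gives c₂ = 1.969.

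**4. Replace c₂ by 1.960, as the article states.**

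| Boundary | t | Interim P | Final P that holds 5% | Overall error if final level is 0.05 |
|---|---|---|---|---|
| Classical | 0.50 | 0.0052 | 0.0480 | 5.20% |
| Lan–DeMets | 0.50 | 0.0031 | 0.0490 | 5.10% |
| Classical | 0.625 | 0.0116 | 0.0459 | 5.38% |
| Lan–DeMets | 0.625 | 0.0092 | 0.0471 | 5.27% |

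**5. Check on binomial data.** Two million simulated trials, 150 then 300 per arm, Pearson chi-square, classical interim boundary:

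| Null rate | Final test alone at 0.05 | Both looks, final 0.05 | Both looks, final 0.0480 |
|---|---|---|---|
| 6% | 5.12% | 5.27% | 4.76% |
| 10.5% | 5.07% | 5.25% | 4.91% |
| 15% | 5.00% | 5.19% | 4.98% |

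The look itself adds about 0.14 to 0.20 points; the rest is the discreteness of the test. With a continuity-corrected test, a proxy for Fisher's exact test, the overall error stays at 3.3% to 4.0%.

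**6. Power cost of the stricter final level**, for 15% against 6%, final test alone, pooled normal formula:

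| Final level | 240 per arm | 300 per arm |
|---|---|---|
| 0.05 | 89.8% | 95.1% |
| 0.0490 | 89.6% | 95.0% |
| 0.0480 | 89.5% | 94.9% |
| 0.0459 (t = 0.625) | 89.1% | 94.7% |

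**7. Who performs the interim analysis.** No arithmetic applies. The sample-size section names the DSMB. Trial organization names the trial management team, and separately has internal members feed the DSMB. The DSMB's listed expertise is critical care, noninvasive ventilation and COPD, with no statistician named. The sections may be describing preparation and review as separate tasks, but the article does not say so.

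**The case against.** **The citation brings its own final boundary, and the exception may cover the look.** The 0.05 sentence is a general convention that does not mention the primary endpoint, and a condensed article may leave numerical levels to the analysis plan. This stands in part: leaving the levels unstated would be no fault. But the article confines the citation to early stopping and states 0.05 for the rest, and the only multiple comparisons it describes are the Bonferroni post hoc tests. Nothing ties the exception to the final primary test.

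**Fisher's exact test is conservative.** True, and if it were used the error would stay below 5%. But at 300 per arm and a rate of 6% the expected count is 300 × 0.06 = 18 per arm, so the ordinary chi-square test would normally apply.

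**The inflation is trivial.** It is small, and this limits the severity. A reader might infer that a full 5% is spent a second time and the error roughly doubles. It does not: the two test statistics are strongly correlated and the interim boundary is strict.

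**The team may only prepare the analysis while the DSMB reviews it.** This is possible. A reader might infer that the chief investigator will see results by arm. The article assigns the team the analysis, not access to results, and it says that all data analyses are done blinded. Coded arms would still show the size of a difference, so the conflict matters, but disclosure is an inference. Nor is this an unblinded trial: it is single-blind, with patients and data collectors blinded and treating investigators not.

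**Conclusion.** The point holds in a limited form. As written, and with the chi-square test, the final rule does not preserve the stated 5%. The overall error is about 5.1% to 5.2% at half information and up to about 5.4% in the extreme case. This rests on reading 0.05 as applying to the final primary test, on an interim boundary of O'Brien–Fleming form, and on the normal approximation, which the simulation supports. At half information a conclusion changes only if the final P falls between 0.048 (classical) or 0.049 (Lan–DeMets) and 0.05.

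The two statements on who performs the interim analysis do conflict and need one answer. The documents do not show that anyone running the trial would see results by arm. Taken together the severity is minor to moderate; the size of the inflation would not justify more.

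**What to change.** **Levels.** Choose one boundary family and state both levels for the primary endpoint, in the interim-analysis section and in the Statistical analysis section:
- classical O'Brien–Fleming: interim P < 0.0052, final P < 0.0480; or
- Lan–DeMets O'Brien–Fleming-type spending: interim P < 0.0031, final P < 0.0490 at half information, both recomputed at the actual information fraction.

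The two should not be mixed, with fixed classical values for a look at exactly half and spending otherwise, because a small shift in timing would then change the rule. The spending form is the easier one to keep if the look may not fall at half. Say also that the general 0.05 level does not apply to the final primary test.

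**Responsibility.** Reconcile the interim-analysis section with Trial organization. State who prepares the interim report, who the three internal members are and whether the data they pass on are by arm. Restrict comparative results to the DSMB and the person preparing its report, separate from those running the trial. Deleting the word interim from the team's duties would not be enough, because the internal members would still supply the DSMB's data.

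**Cost.** A few sentences and no extra patients. At half information the power loss is about 0.2 to 0.3 points with 0.0480 and about 0.1 to 0.2 with 0.0490. An independent statistician for the interim report may have to be named.
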